### Confidentiality {27}

Survey participants will be assured of the confidentiality of the survey process before they give consent. The survey team will ensure a private setting for interviews to be conducted. Any data passed on to researchers will only be identified by a unique personal number to ensure anonymity. Only data administrators will have access to identifying information.

#### Plans for collection, laboratory evaluation, and storage of biological specimens for genetic or molecular analysis in this trial/future use {33}

There will be no biological specimens involved in this trial.

## Statistical methods

### Statistical methods for primary and secondary outcomes {20a}

Descriptive statistics for each treatment arm at baseline will summarize sociodemographic characteristics as means, percentages, or counts with standard deviations. The primary outcome will be assessed as the difference in renewal rates between each treatment and its corresponding control group, comparing the difference between those who received renewal reminders (1R, 2R) or autorenewal prompts (1A, 2 A, 3 A) against the respective control group (1C, 2 C, 3 C). Specifically, we compare 1R vs. 1 C, 1 A vs. 1 C, 2R vs. 2 C, 2 A vs. 2 C, and 3 A vs. 3C. The primary outcome is rate of successful renewals in each group. The primary endpoint is the effect size, estimated with a logistic regression of treatment status on insurance outcome, and reported as an odds ratios with significance levels (*p* values and 95% confidence intervals). To assess whether reminders resulted in less or in shorter coverage gaps, we will conduct a duration analysis, comparing time-to-renewal between the treatment arms using Kaplan–Meier curves and Weibull regressions. All effect sizes will represent an intent-to-treat (ITT) effect, as we cannot be certain if a treatment reached the intended recipient. The secondary outcomes will be assessed using descriptive statistics and logistic regressions in order to compare the likelihood of signing up for autorenewal, and the likelihood of a successful renewal occurring, conditional on having signed up for autorenewal, across the different expiration date groups. The results will be reported as absolute differences and odds ratios. We cluster-randomize individuals by phone number in order to avoid having individuals with the same phone number in different treatment arms, which could result in spill-overs. For the analysis, we use individual-level analysis for two reasons: (1) because the treatment is addressed to each individual and timed according to individuals’ expiration dates, making this an individual-level treatment, and (2) ~ 85% of phone number clusters contain only one individual, making an application of a mixed-effects model difficult, as there would be nearly as many random intercepts as there are observations. However, we do use clustered standard errors in the analysis to account for possible intra-cluster correlations.

The quantitative follow-up survey data will be analyzed using descriptive statistics showing the distribution to responses to answers across the Likert scale, and logistic regressions of sociodemographic factors on reported outcomes.

The qualitative scale-up interview data will undergo a thematic analysis with ATLAS.ti 22. The interview transcripts will be coded independently to validate and confirm the coding strategy. The codes will be sorted into themes and subthemes and refined into a narrative. A combination of deductive and inductive methods will be applied for data analysis. Deductive reasoning will be guided specifically by using the Predisposing, Need, and Enabling Framework and other existing literature on the factors influencing the implementation and potential use of mobile technology [9, 34, 35].

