## Introduction

### Background and rationale {6a}

Ghana implemented its National Health Insurance Scheme (NHIS) in 2004 in order to improve coverage and expand access to health care. While 82% of Ghanaians did register for NHIS membership at some point since the scheme’s inception, overall population coverage remains relatively low at about 52% of the population [1, 2]. Similar to health insurance schemes in other African countries, the NHIS relies on a system of annual re-enrolment of members [3]. This means that individuals have to actively renew their membership and, depending on their exemption status, may have to pay an annual premium and processing fee [2]. Members can renew their membership within 90 days before expiration. After the expiration date, there is a 90-day grace period in which the member can renew their membership without penalty and be able to instantly access care. After more than 90 days, the member can still renew but has a 30-day waiting period before insurance becomes active. This is done to discourage the likelihood of adverse selection of renewing health insurance only when needed. Children under 5, pregnant women, and elderly over 70 are exempt from this waiting period.

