### Secondary outcomes

**Table Tabg:** 

Outcomes	Analysis Metric	Method of aggregation	Time point
Renewal by expiration date (by t_0_), renewal without coverage gap (by t_90_)	Odds ratio between treatment and control group for each arm	Proportion succeeding in renewing insurance coverage by date	End of observation period
Coverage gap	Time ratio between treatment and control group for each arm	Mean length in days/duration until renewal	End of observation period
Acceptance of autorenewal option	Odds ratio between treatment and control,	Proportion signing up for autorenewal	End of observation period
Successful renewal via autorenewal	Odds ratio between treatment and control	Proportion of autorenewal set-ups resulting in a successful renewal	End of observation period
User experience and acceptability of intervention	Agreement with questions regarding usefulness and usability of intervention	Proportion of individuals agreeing with statements	Follow-up survey Post-intervention period

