## Data collection and management

### *Plans for assessment and collection of outcomes* {18a}

Anonymized routine data of all trial participants is extracted from the NHIS database, and shared with the researchers. This contains the renewal transaction data of NHIS members (date of transaction, beginning and end of insurance period, fees paid, platform used for transaction), intervention status (trial arm, autorenewal registration status, opt-out status), and user information (unique identifying number, age, gender, marital status, payment category) for each participant. This data is used to assess rates of insurance renewal and of autorenewal enrolment across treatment arms and demographic subgroups.

In addition, a randomly selected sample of 280 households in Kumasi will be surveyed as part of the quantitative and qualitative follow-up survey assessing user experience, acceptability, and usability of the reminder and autorenewal service. These households are part of the verified sample and were previously surveyed in 2023 as part of a preliminary implementation and feasibility study, and will be surveyed again after the intervention is completed. The data will be collected by trained research assistants through face-to-face interviews. The quantitative follow-up survey will collect sociodemographic characteristics of households and individuals, health insurance coverage status, satisfaction with the reminders, and autorenewal option.

For the qualitative scale-up interviews, data will be collected using a semi-structured approach based on interview guides. The interview guide used for data collection will be prepared based on existing literature and the research objectives of the study.

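### The coverage-gap outcome is measured as time to renewal, which is not the coverage gap under the protocol's own grace-period and waiting-period rules

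*Protocol article*

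**What the plan says.** The secondary outcomes table gives coverage gap the effect measure "Time ratio between treatment and control group for each arm" and the aggregation "Mean length in days/duration until renewal". Gap length and time to renewal are thus entered as one quantity. The section on statistical methods {20a} carries this through: "To assess whether reminders resulted in less or in shorter coverage gaps, we will conduct a duration analysis, comparing time-to-renewal between the treatment arms".

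The row above in the same table defines a binary outcome, "renewal without coverage gap (by t_90"), so any renewal up to day 90 after expiry is gap-free.

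The scheme rules are in Background and rationale {6a}. Renewal opens 90 days before expiry. After expiry "there is a 90-day grace period in which the member can renew their membership without penalty and be able to instantly access care". Later than that, "the member can still renew but has a 30-day waiting period before insurance becomes active", with exemptions for children under 5, pregnant women and people over 70.

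The data extract described under {18a} includes, for each transaction, the "beginning and end of insurance period".

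**The concern.** Reducing coverage gaps is one of the two effects named in Objective 1, and this is the only outcome that measures how long gaps last. If the measured duration is not the gap, a time ratio reported under that label answers another question, namely how quickly members renew.

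The two quantities part company in three places: among grace-period renewers, among renewers after day 90, and among members who renew before expiry. The first two follow from the text whatever starting point the duration analysis uses. The third takes a different form depending on that starting point, but none removes it.

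**Working it through.** The plan gives no figure to reproduce for this outcome, so the check applies the scheme rules in {6a} to the outcome definitions.

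**Step 1: map renewal day to gap.** Let *t* be the renewal day counted from expiry, for a non-exempt member. The text allows two readings of the grace period.

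- Reading A: grace days count as covered, as the binary outcome's label implies. The gap is 0 for *t* ≤ 90. For *t* > 90, cover restarts at *t* + 30, which is (*t* + 30) − 90 = *t* − 60 days after grace ends.
- Reading B: the member is uncovered until renewal. The gap is 0 for *t* ≤ 0, *t* for days 1 to 90, and *t* + 30 after day 90.

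| Renewal day *t* | Time to renewal from expiry | Gap, reading A (from end of grace) | Gap, reading B (from expiry) | Binary outcome says |
|---|---|---|---|---|
| −60 | −60 | 0 | 0 | no gap |
| 0 | 0 | 0 | 0 | no gap |
| 45 | 45 | 0 | 45 | no gap |
| 90 | 90 | 0 | 90 | no gap |
| 91 | 91 | 31 | 121 | gap |
| 120 | 120 | 60 | 150 | gap |

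Under reading A, time to renewal is wrong at every *t* > 0. Under reading B it is right for days 1 to 90, but the binary label is then wrong, and durations after day 90 are 30 days too short. Neither reading makes the two table rows and the waiting period agree.

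**Step 2: members who renew on time.** {6a} and the text after it say about 50% of insurance periods are renewed late or never, so about 100 − 50 = 50% are renewed on time. Their gap is zero.

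- Clock at expiry: their time is zero or negative, which a Weibull model cannot use.
- Clock at day −90: two members renewing on days −80 and −10 have durations of 10 and 80 days, yet both have a gap of zero. The ratio then measures speed of renewal.

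**Step 3: how much the definition matters (illustration only).** Weibull models were fitted to simulated data, 100,000 per arm, censored at day 180 after expiry. The control split combines the background rates, assuming that the 40% with gaps in the Abstract includes the 19% who never renew: 50% on time, 60 − 50 = 10% in grace, 40 − 19 = 21% later, 19% never. The treated split (54/10/18/18%) is assumed. Renewal days are uniform within bands, with late renewals spread over days 90 to 365. For the gap rows, renewal up to day 90 scores 0 and later renewal scores *t* + 30.

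| Definition applied to the same data | Time ratio |
|---|---|
| Clock at day −90, everyone | 0.89 |
| Clock at expiry, on-time renewers dropped | 0.96 |
| Clock at expiry, on-time renewers set to 0.5 day | 0.70 |
| Clock at expiry, on-time renewers set to 0.01 day | 0.56 |
| Rule-based gap, positive gaps only | 1.01 |
| Rule-based gap, zeros set to 0.5 day | 0.66 |

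With late renewals spread over days 90 to 180 instead, the same six definitions run from about 0.7 to about 1.0. These are not forecasts. They show that the ratio depends heavily on choices that the label coverage gap does not settle.

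**The case against.** **The starting point and the handling of early renewers may sit in a full protocol or analysis plan.** This stands. The article states no time origin and no deletion rule, and that silence is not a finding. A reader might infer that half of Group 1 will be excluded and the time ratio biased against the intervention. The document does not support this: it needs a clock at expiry plus deletion of non-positive times, neither of which is written, and {20a} commits to intention-to-treat effects.

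**The excluded share might be put at up to 60%.** That mixes two groups. About 50% have no positive time from expiry. About 60% have no gap, which on the assumption in Step 3 includes grace-period renewers with positive times. Both are background rates, not Group 1 data.

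**In the grace period, access follows renewal, so days to renewal may be a fair gap measure.** This is reading B. It is tenable, but it contradicts the day-90 label and still omits the 30-day wait.

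**Whether gaps are fewer is already tested by the binary outcome.** True, and it limits the consequence to gap length.

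**A mean is not estimable with never-renewers, and a Weibull hazard is too rigid.** Neither carries much weight. Never-renewers can be censored, the effect measure is a time ratio, and Kaplan–Meier curves are planned alongside.

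**Group 2 has already expired at the start, so on-time renewal cannot arise there.** Correct. Group 3 expires only after the planned end of the intervention. The point is therefore put for Group 1.

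**Conclusion.** The concern holds for the definition of a secondary outcome. The article equates coverage gap with duration until renewal, and its own rules make them different. A renewal on days 1 to 90 is both gap-free and up to 90 days long. A non-exempt renewal after day 90 restores cover 30 days later than the measured time. For the roughly half of periods renewed on time, the gap is zero and a time ratio cannot express it for all randomised members.

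The first two parts rest only on the article's text. The size of the third rests on a background rate that may differ in Group 1. No direction of bias is established, and no loss of randomised members is stated. The primary logistic analysis is not affected. The change should be made before gap results are reported.

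**What to change.** For Group 1:

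1. Define coverage gap as the number of days without active insurance in a fixed window after expiry, derived from the recorded insurance dates. On-time renewers score 0, and the waiting period is included where it applies.
2. State one rule for grace-period days. Either they count as covered, in agreement with the day-90 binary, or they count as uncovered and that binary is renamed renewal within the grace period. The label also appears in the primary outcome table; renaming it there changes no data.
3. Choose a window fully observed for every member, or treat shorter follow-up as censoring, for example with a restricted mean. Members expiring late in the intervention should not be scored as full-window non-renewers merely because follow-up ended.
4. Compare mean uncovered days between randomised arms as a difference with a cluster-robust 95% confidence interval.
5. Keep the Kaplan–Meier and Weibull analyses, labelled as time to renewal.

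The cost is some wording and one derived variable from dates already extracted. The gap effect would be reported in days, not as a ratio.

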### Interim analyses {21b}

Opt-out requests and autorenewal sign-ups will be monitored to assess error-free functioning of the reminder and autorenewal system, and to warn of any logistical or technological problems which may occur at larger-scale implementation.

### Methods for additional analyses (e.g., subgroup analyses) {20b}

The timing of the reminders relative to expiration date creates a staggered increase of treatment intensity at the beginning of the trial, and a decreasing intensity toward the end of the trial. In order to account for varying treatment intensity, we control for whether the full or a partial treatment was received by the participant. For this, we conduct sensitivity analyses which include binary and categorical variables in the logistic regression which denote the treatment intensity or variation received by a participant. This allows us to estimate an adjusted treatment effect, and to assess the marginal impact of an additional reminder message. In addition to the full and partial treatment effects, we will also estimate treatment effects for different sociodemographic subgroups using multiple logistic regressions controlling for gender, age group, and payment category.

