**Table Taba:** 

Message #	1	2	3	4	5	6
t_x_	t_−28_	t_−7_	t_0_	t_+30_	t_+60_	t_+89_
Condition	Membership has not been renewed by t_x_					
Message	Dear Firstname Lastname, Your NHIS card will expire in *4 weeks*. You can renew using the MyNHIS app, *929# or go to the nearest NHIA district office	Dear Firstname Lastname, Your NHIS card will expire in *1 week*. You can renew using the MyNHIS app, *929# or go to the nearest NHIA district office	Dear Firstname Lastname, Your NHIS card expires *TODAY*! You can renew using the MyNHIS app, *929# or go to the nearest NHIA district office	Dear Firstname Lastname, Your NHIS card is expired. You can renew within 60 days to avoid a 1-month wait. Use MyNHIS app, *929# or go to the NHIA district office	Dear Firstname Lastname, Your NHIS card is expired. You can renew within 30 days to avoid a 1-month wait. Use MyNHIS app, *929# or go to the NHIA district office	Dear Firstname Lastname, Your NHIS card is expired. You can still renew today to avoid a 1-month wait. Use MyNHIS app, *929# or go to the NHIA district office

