**Table Tabb:** 

Message #	7
Day of trial	Day 1 and Day 30 of Trial
Condition	Membership has expired and has not been renewed
Message	Dear Firstname Lastname, Your NHIS card expired dd/mm/yyyy. You can use the MyNHIS app, *929# or go to the NHIA district office to renew your coverage

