
Due to the long run-time of the full treatment protocol (90 days for autorenewal, 120 days for reminders before and after expiration date), not all individuals will receive the full treatment. Individuals with expiration dates less than 30 (7, 1) days before trial start will not receive the t-30 (t_−7_, t_−1_) day reminder. Individuals whose expiration date is less than 60 (30) days away from the end of the intervention will not receive the t_+60_ (t_+30_) reminders. Furthermore, as individuals only receive the autorenewal savings reminders by signing up for the autorenewal system, those with expiration dates less than 90 or 60 days after sign-up will not receive the t_−90_ or t_−60_ savings reminder. We therefore expect that the aggregate treatment effect for the full trial sample will underestimate the actual treatment effect, as some individuals in the trial will not have received all messages due to these timing constraints. This will be addressed through subgroup and sensitivity analyses, which compares the outcomes for those who received the full treatment or a variation of a shortened treatment.

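### The treatment-intensity analysis is worded on treatment received, which depends on not having renewed or on signing up; it should be defined from the expiry date and trial calendar alone

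*Protocol article*

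**What the plan says.** Methods for additional analyses {20b} states "we control for whether the full or a partial treatment was received by the participant". It does this through sensitivity analyses "which include binary and categorical variables in the logistic regression which denote the treatment intensity or variation received by a participant". Two results are promised: an adjusted treatment effect, and the ability to "assess the marginal impact of an additional reminder message". The discussion section, Explanation of design choice, expects the aggregate effect to be an underestimate because some members miss messages. It relies on analyses "which compares the outcomes for those who received the full treatment or a variation of a shortened treatment" to address this.

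The intervention description sets the sending rules. All six messages in the Arm 1R table carry the condition "Membership has not been renewed by" the day of the message. The repeated message in the Arm 2R table carries the condition "Membership has expired and has not been renewed". In the autorenewal arms, the savings reminders go only to members who have opted in.

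The primary outcome table covers renewal by expiry, renewal without a gap, and any renewal. Statistical methods {20a} makes all effect sizes intention-to-treat.

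**The concern.** A member who renews early stops receiving reminders, while a member who never renews receives every reminder the calendar allows. The number received is therefore partly a record of the outcome. With it in a logistic model for renewal, more messages go with fewer renewals, whatever the messages do.

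In the autorenewal arms the savings reminders depend on sign-up, a choice made after randomisation by members who probably differ from the rest. The article does not say what value control members take. If they are coded as having received nothing, the variable also coincides with arm.

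At stake is the analysis meant to correct an expected underestimate and to advise on how many reminders to send. Taken literally, it could report useful reminders as harmful.

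**Working it through.** The plan gives no figure for this analysis, so there is none to reproduce. The check has four steps.

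**1. Inputs.** The Background says about 50% of periods are renewed late or not at all, so 50% are renewed by expiry (t0). The Abstract says 40% have gaps and 19% never renew; this is taken as 60% renewed by day 90 and 81% ever. Assumptions: renewal days are uniform within days −90 to 0, 1 to 90 and 91 to 180, and messages have no effect.

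**2. Arithmetic for a 1R member for whom all six messages fall inside the trial.**
- Daily renewal share in days 1 to 90: 0.10/90 = 0.0011.
- Not renewed by day +89, so sent the sixth message: 0.40 + 0.0011 = 0.4011.
- Renewed by day 90, given six messages: 0.0011/0.4011 = 0.3%. Given fewer than six: 100%.
- Renewed by day 180, given six messages: (0.21 + 0.0011)/0.4011 = 52.6%. Given fewer than six: 100%.
- Renewed by t0: 100% of those sent 0 to 2 messages. Among those sent three or more it is 0% if expiry-day renewals precede the message. If they all follow it, it is (0.50/91)/(0.50 + 0.50/91) = 0.0055/0.5055 = 1.1%.

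**3. Simulation with expiry dates spread over the trial.** There were 40,000 members each in 1R and 1C, and expiry dates were uniform over 184 days (an assumption). The received count was fitted within 1R. The calendar count, meaning the messages the dates would allow regardless of renewal, was computed in both arms and fitted with its arm interaction.

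| Outcome | ITT odds ratio | Odds ratio per message received | Arm × calendar count, odds ratio (p) |
|---|---|---|---|
| By t0 | 1.007 | 0.003 | 1.014 (0.28) |
| By day 90 | 1.006 | 0.22 | 1.019 (0.15) |
| Any (to day 180) | 1.019 | 0.49 | 1.007 (0.65) |

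By day 90, renewal was 100% among those sent 0 to 2 messages, 40% with three, 28% with four, 14% with five and 0.2% with six. If all six messages are schedulable for everyone, the received count separates renewal by t0 perfectly.

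**4. Does calendar timing explain the variation in each arm?**
- 1R: yes in part. Expiry near the start or end of the trial cuts off messages, and this is fixed before randomisation.
- 2R: no. Messages are sent on Day 1 and Day 30 for everyone. The number received can differ only through renewal before Day 30, opt-out or technical failure.
- 1A: no. Explanation of design choice counts the 90- and 60-day cut-offs from sign-up.

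The offsets also differ. The Arm 1R table has t−28, t−7, t0, t+30, t+60 and t+89. Explanation of design choice names t−30, t−7, t−1, t+30 and t+60. Its phrase "Individuals with expiration dates less than 30 (7, 1) days before trial start will not receive" literally describes members whose insurance had already expired, who belong to Group 2.

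**The case against.** A reader might infer that the trial will certainly enter realised message counts. The article does not say so. Section {20b} opens by tracing the variation to reminder timing relative to the expiry date. Explanation of design choice lists who misses which reminder by distance from the trial's start or end, and never gives early renewal as a reason. Built that way, the 1R variable is a baseline quantity and returns the null, as the last column of the table shows. The list of routine data in {18a} contains no message log. How controls are coded is the kind of detail an analysis plan may settle.

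Most of this stands, and reverse causation cannot be asserted as what will be done. It does not remove the point. The wording is treatment received in both sections, and a received count could be rebuilt from renewal dates, which carry the outcome directly. The calendar reading has no content in 2R and does not describe the autorenewal savings reminders.

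A reader might also infer that the mismatched offsets greatly change how many members count as fully treated: (184 − 28 − 89)/184 = 36% against (184 − 30 − 60)/184 = 51%. This is not supported. It assumes 184 days, whereas the Trial status dates, 20 May to 31 December 2024, span 225. It also treats listed examples as the definition of full treatment. The same section gives 120 days for the full reminder protocol, and (184 − 120)/184 = 35%. The offsets are a drafting inconsistency to reconcile, with no size attached.

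Nor is renewal by t0 necessarily exactly 0% among those sent the expiry-day message, since they can renew that day.

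**Conclusion.** The point holds as a fault in how the analysis is specified. As worded, the rule admits a covariate determined by the outcome (1R, 2R) or by sign-up (autorenewal arms), and attaches a per-message claim to it. Under that literal reading the bias is large enough to make inert messages look strongly harmful. The exact odds ratios depend on the assumed timing of renewals and spread of expiry dates, and the 0.003 is close to perfect separation. The direction follows from the sending rule alone.

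Under the calendar reading of 1R the bias disappears, but the text does not restrict the variable to that reading. The damage is confined to the sensitivity analyses and the conclusions on message number. The primary intention-to-treat comparisons between arms are unaffected.

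**What to change.** 1. For Group 1, derive intensity only from the baseline expiry date and the trial start and end dates: the messages the calendar would allow, regardless of renewal or sign-up.
2. Assign it identically in treated and control arms. For 1A versus 1C, which has its own message schedule, use time from Day 1 to expiry.
3. Fit arm, schedulable intensity and their interaction, and report the arm effect within each category. Expiry date is not randomised, so differences between categories may also reflect calendar time and length of follow-up.
4. Do not estimate a per-message effect from realised message counts, and do not run a received-intensity analysis in Group 2.
5. Reconcile the day offsets and the trial-start wording in Explanation of design choice with the Arm 1R table before defining full treatment.

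The cost is revised wording, one derived variable from insurance-period dates that {18a} already lists, and some loss of precision within categories.

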#### Arm 1A

**Table Tabd:** 

Message #	9	10	11	12
t_x_	t_−90,_ t_−60_	t-_31_	t_−30, t-29, t-28,_	t_−27_
Condition	Member has opted into autorenewal. Active membership has not been renewed. The member is required to pay premium or processing fee		Autorenewal payment has failed	Autorenewal payment has failed 4 times
Message	Dear Firstname Lastname, your NHIS insurance automatically renews on dd/mm/yyyy. Please make sure you have xx cedis in your MoMo account (Dial *929*20# to change your settings)	Dear Firstname Lastname, your NHIS insurance automatically renews in one day. Please make sure you have xx cedis in your MoMo account (Dial *929*20# to change your settings)	Dear Firstname Lastname, unfortunately, your membership could not be renewed. We will try again tomorrow. Please make sure you have xx cedis in your MoMo account (Dial *929*20# to change your settings)	Dear Firstname Lastname, your membership could not be renewed automatically Please use MyNHIS app, *929# or go to the nearest NHIA district office

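### The treatment-intensity sensitivity analyses condition on messages received, but renewal itself stops the messages, so a useless reminder would show large spurious effects

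*Protocol article*

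**What the plan says.** The section on additional analyses {20b} explains that reminder timing relative to expiry and trial dates makes treatment intensity vary, and answers: "we control for whether the full or a partial treatment was received by the participant". The sensitivity analyses will "include binary and categorical variables in the logistic regression which denote the treatment intensity or variation received by a participant". Their stated products are an adjusted treatment effect and a means "to assess the marginal impact of an additional reminder message".

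The Discussion (Explanation of design choice) expects the aggregate effect to be an underestimate, because timing constraints keep some members from getting every message. It says this will be addressed by an analysis which "compares the outcomes for those who received the full treatment or a variation of a shortened treatment".

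The intervention tables give the sending rules. In arm 1R, six reminders fall at t−28, t−7, t0, t+30, t+60 and t+89, each on the condition "Membership has not been renewed by" the day in question. In arm 2R the condition is "Membership has expired and has not been renewed". In arm 1A, messages 9 and 10 require: "Member has opted into autorenewal. Active membership has not been renewed"; messages 11 and 12 follow failed automatic payments.

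The outcome in the logistic model is renewal: by expiry, without a coverage gap (by t90), or at all (Outcomes {12}).

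**The concern.** Renewal is the outcome, and renewal ends the messages. A member who renews early gets few reminders because of having renewed; a member can get all six only by still being unrenewed at t+89. A covariate for messages received therefore carries the outcome into the right-hand side of the model, and a larger sample does not cure this. In arm 1A the later messages also depend on a voluntary opt-in made after randomisation, a second way in which receipt is not fixed at baseline.

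At stake are two results for which this is the stated method: the adjusted effect that is to address the expected underestimate, and the value of an extra reminder, which bears on how many messages a national service should send.

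**Working it through.** The protocol gives no figure for this analysis, so there is none to reproduce. The check has three parts.

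**1. What follows from the sending rules alone** (arm 1R, leaving aside opt-outs and technical failures)

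- Sent all six: unrenewed at t+89, so renewal by t0 is 0% whatever the true effect.
- Sent none: every Group 1 member expires inside the intervention period and is due at least the t0 message, so a count of zero means renewal by t0, i.e. 100%.
- Due all six by calendar but sent fewer: already renewed, i.e. 100%.

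Controls are sent no reminders. In a model with arm and message count, the arm coefficient therefore contrasts controls with reminder-arm members at count zero, who have all renewed.

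With a 180-day period, all six can be sent only if expiry lies at least 28 days after the start and 89 days before the end: (180 − 28 − 89)/180 = 63/180 = 35% of Group 1.

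**2. Simulation with no reminder effect**

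Inputs from the documents:
- about 50% renewed by expiry (Background: about half of periods are renewed late or never);
- 60% by t+90 (Abstract: 40% have gaps);
- 81% ever (Abstract: 19% fail to renew).

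Assumptions:
- renewal times uniform within −90 to 0 (50%), 0 to 90 (10%) and 90 to 365 days (21%), with 19% never;
- expiry uniform over the period; members included only if unrenewed at the start; observation ends with the intervention;
- period of 183 days (six months) or 225 days (20 May to 31 December 2024, from Trial status).

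Messages go out only inside the window and only before renewal.

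For renewal by t+90 among those sent all six, the arithmetic is direct. Only the last day remains: 10% × 1/90 = 0.11% of members, out of 40% + 0.11% still unrenewed at t+89, so 0.11/40.11 ≈ 0.3%.

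| Quantity (true OR = 1) | 183 days | 225 days |
|---|---|---|
| Share of 1R sent all six | 16% | 21% |
| Renewed by t0: control / all six / fewer | 43% / 0% / 52% | 45% / 0% / 57% |
| Renewed by t+90: control / all six / fewer | 52% / 0.2% / 62% | 53% / 0.3% / 68% |
| Arm-only (ITT) OR | 1.00 | 1.00 |
| By t+90, arm + count: arm OR; OR per message | 117; 0.20 | 111; 0.22 |
| Any renewal, arm + count: arm OR; OR per message | 48; 0.28 | 35; 0.33 |

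For renewal by t0 the fit is close to separation and its estimates carry no meaning.

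Other timing assumptions move the values. With 50% or 60% on time, exponential delays of mean 30 to 90 days and a 180-day period, the arm OR for any renewal is about 52 to 218 and the per-message OR 0.17 to 0.28. If the first renewal pattern is followed for a full year after expiry, the any-renewal figures fall to about 12 to 14 and 0.5. In every case the arm OR is far above 1 and the per-message OR well below 1.

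Coding intensity as full or partial instead of a count does not help. In the exponential-delay runs, the OR for any renewal against control is 0.01 to 0.04 for full receipt and 1.38 to 1.46 for partial receipt.

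**3. The same null data with intensity taken from the schedule**

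In the exponential-delay runs, members of both arms were classed by the messages their expiry date allowed, and arm was compared with control within class. The OR is 1.00 to 1.01 for the full schedule and 1.00 for the partial schedule, on all three outcomes. The artefact disappears.

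**The case against.** The best reply is that the authors meant scheduled intensity. Section {20b} opens with reminder timing relative to expiry, and the Discussion lists which expiry dates miss which messages. For arm 1R those classes are fixed by the calendar, so *received* may be loose wording. This is plausible. But receipt is the stated exposure in both places, neither place notes that renewal also ends the messages, and a per-message effect is an explicit aim. An analyst following the text would code receipt.

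A reader might go on to infer that the scheduled reading fails too, because treated classes would be set against all controls. The protocol does not say so: section {20a} compares each arm with its own group's control, and coding the class in the control arm may be left to an analysis plan that is not shown. A pooled control would give, under no effect, ORs for any renewal of 1.14 to 1.34 (full schedule) and 0.87 to 0.93 (partial) in the exponential-delay runs, where observation ends with the intervention. That is a reason to specify the control coding, not an error in the plan.

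It can also be said that these are only sensitivity analyses. That stands: section {20a} fixes the primary analysis as intention to treat. It limits the severity of the fault without removing it.

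**Conclusion.** The concern holds for the analysis as worded. Conditioning on messages received would produce large false effects from a useless reminder: an arm OR of roughly 35 to 120 and a per-message OR of roughly 0.2 to 0.33, for renewal by t+90 and for any renewal. These figures rest on the first set of timing assumptions, with observation ending at the end of the intervention. The 0% renewal by t0 among those sent all six follows from the sending rule alone, and the direction held in every scenario tried.

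Two stronger readings are not supported. One is that the odds ratios run to infinity and zero in general. That needs every member to be able to receive all six messages; the trial window prevents this, and the estimates for two of the three outcomes are finite. The other is that the trial's main conclusion is contaminated. The Discussion says the expected underestimate will be addressed by subgroup and sensitivity analyses, not that the primary estimate will be replaced, and the ITT odds ratio in the simulation is 1.00.

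**What to change.** In section {20b} and in the Discussion, replace *received* with *scheduled*, and state that:

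- the intensity class is derived only from expiry date and trial start and end dates, as the set of messages a member would have been due had they never renewed;
- control members get the same class as treated members, and in 1A the class comes from expiry date, not from sign-up;
- arm is compared with control within each class, through an arm-by-class interaction;
- the value of extra messages is read only as a difference between these within-class effects;
- messages actually sent or received are not entered as a covariate.

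Before class limits are set, the message days need reconciling: the Discussion names t−30 and t−1 reminders, while the 1R table has t−28 and t0.

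The cost is wording and a little programming. Expiry dates already define the groups, and insurance-period dates are in the routine extract, so no new data are needed. The intervention has ended, but this changes only the analysis. The price is wider intervals within classes: on the 180-day reckoning only about 35% of Group 1 falls in the full-schedule class.
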